### Sample size

The sample size was calculated based on the EASI_50_ achievement rate at week 4, which was defined as the proportion of patients who achieved ≥50% improvement in Eczema Area and Severity Index (EASI) score from baseline to week 4. According to preliminary observation data, we assume that the EASI_50_ achievement rate at week 4 would be 85% in the treatment group and 50% in the control group. Based on a 2:1 randomization ratio, the sample size is calculated with PASS 15.0 software. Setting a two-tailed *α* level at 0.05 and statistical power at 80%, the calculation yields a requirement of 40 patients for the treatment group and 20 for the control group. Considering a 10% dropout rate, the final enrollment target is set at 44 patients for the treatment group and 22 patients for the control group. The specific formula for calculating sample size was as follows:
$$n_{2}=\frac{\frac{p_{1}\times (1-p_{1})}{k}+p_{2}\times (1-p_{2})}{{\left(p_{1}-p_{2}\right)}^{2}}\times {\left(\mu_{\alpha /2}+\mu_{\beta }\right)}^{2},n_{1}=k\times n_{2}$$

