#### Secondary outcomes

The secondary outcome indicators include the EASI, Visual Analogue Scale (VAS), Investigator’s Global Assessment (IGA), and Dermatology Life Quality Index (DLQI) (23, 24). These indicators will be assessed at baseline (week 0) and subsequently at weeks 1, 2, 4, and 16. A detailed study schedule is presented in Table 1, which specifies the evaluation time points for each measure.

**Table 1 tab1:** Study schedule of the MuShengshu clinical trial (16 weeks).

Indicator	Baseline	Follow-up			
	Visit 1 (week 0)	Visit 2 (week 1)	Visit 3 (week 2)	Visit 4 (week 4)	Visit 5 (week 16)
Informed consent	✓	–^a^	–	–	–
Demographic features	✓	–	–	–	–
Family medical history	✓	–	–	–	–
Physical examination	✓	–	–	–	–
Inclusion/exclusion criteria check	✓	–	–	–	–
Randomization	✓	–	–	–	–
EASI^b^	✓	✓	✓	✓	✓
VAS^c^	✓	✓	✓	✓	✓
IGA^d^	✓	✓	✓	✓	✓
DLQI^e^	✓	✓	✓	✓	✓
Concomitant medications	–	✓	✓	✓	✓
Adverse events	–	✓	✓	✓	✓

a Not applicable.

b EASI: Eczema Area and Severity Index.

c VAS: Visual Analogue Scale.

d IGA: Investigator’s Global Assessment.

e DLQI: Dermatology Life Quality Index.

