### Statistical analysis

In this study, data analysis will be conducted using the SAS 9.4 statistical software. Normally distributed quantitative variables will be summarized as mean and standard deviation (SD), while skewed distributions will be represented by the median and interquartile range (IQR). For inter-group comparisons of quantitative variables with normal distribution, the Student *t*-test will be utilized, whereas the Wilcoxon rank-sum test will be applied for skewed quantitative data. Repeated measurement data will be analyzed using repeated measures analysis of variance. Categorical variables will be presented as frequencies and proportions (%), with differences between groups evaluated through chi-square tests or Fisher’s exact tests.

Data analysis in this study will follow the intention-to-treat (ITT) principle, including all randomized participants regardless of adherence to the protocol or completion of the study (28). Missing data will be addressed under the missing-at-random assumption using sequential regression multiple imputation, which estimates missing values based on regression models that consider the relationships among all other variables (29). Furthermore, analyses will be performed on both the full analysis set (FAS) and the per-protocol set (PPS), with a *p*-value of less than 0.05 (two-tailed) is viewed as statistically significant.

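### The continuous secondary outcomes are compared without adjustment for the week-0 score, which costs precision that the trial's own data could supply

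*Protocol article*

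**What the plan says.** The Statistical analysis section sets one general rule for measured variables. "For inter-group comparisons of quantitative variables with normal distribution" it names the Student t-test, with the Wilcoxon rank-sum test where data are skewed. For longitudinal data it adds: "Repeated measurement data will be analyzed using repeated measures analysis of variance". It names no covariate, neither the baseline score nor the stratification factors (gender and severity, from the Randomization section).

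Of EASI, VAS, IGA and DLQI, the Secondary outcomes section says: "These indicators will be assessed at baseline (week 0) and subsequently at weeks 1, 2, 4, and 16". Table 1 and the Data collection and management section agree, so the baseline value is part of the planned data for every patient.

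Three things are not stated: whether the t-test or Wilcoxon test uses the visit value or the change from baseline, whether week 0 is a level of the time factor, and whether the group effect or the group-by-time interaction is the test of treatment.

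**The concern.** The control arm is planned at 22 patients, of whom about 20 are expected to be evaluable, so precision on the secondary scales is scarce. Scores on the same scale in the same patient are normally correlated over time. A two-sample test on the visit value leaves that part of the variation in the error term. A baseline-adjusted comparison removes it and also corrects for chance imbalance in the starting score.

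At stake are the width of the confidence intervals and the chance of detecting a real difference in EASI, VAS or DLQI. Repeated measures analysis of variance raises a second, conditional question: whether a visit at which treatment cannot yet have acted is averaged into the reported effect.

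**Working it through.** **Inputs from the protocol article.** Two-sided alpha 0.05 (Statistical analysis); a "requirement of 40 patients for the treatment group and 20 for the control group" (Sample size); five assessment times, four of them after baseline (Secondary outcomes).

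**Assumed inputs.** The article gives no SD, correlation or effect size for the secondary scales. I take equal SDs at all visits, an equal correlation r between visits of 0.3, 0.5 or 0.7, and a true difference of 0.70 SD.

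**The plan's own figure.** The EASI50 rate "would be 85% in the treatment group and 50% in the control group". With the printed formula and k = 2, n2 = [0.85 × 0.15/2 + 0.50 × 0.50] / 0.35² × (1.960 + 0.842)² = 0.31375/0.1225 × 7.849 = 20.10. The pooled-variance formula gives exactly 20 and 40. The stated size reproduces and concerns the primary outcome only.

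**One visit: variance relative to the unadjusted visit value.** Analysis of covariance: 1 − r². Change score: 2(1 − r).

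| r | Visit value | Change score | Baseline-adjusted | Equivalent patients, 1/(1 − r²) |
|---|---|---|---|---|
| 0.3 | 1.00 | 1.40 | 0.91 | × 1.10 |
| 0.5 | 1.00 | 1.00 | 0.75 | × 1.33 |
| 0.7 | 1.00 | 0.60 | 0.51 | × 1.96 |

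Testing change scores therefore does not recover the full gain at any of these values.

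**Detectable difference at 80% power.** Unadjusted: 2.802 × √(1/20 + 1/40) = 2.802 × 0.2739 = 0.77 SD. Multiplying by √(1 − r²) gives 0.73, 0.66 and 0.55 SD.

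**Power at 0.70 SD.** Unadjusted: Φ(0.70/0.2739 − 1.96) = Φ(0.596) = 72%. Dividing the standard error's variance by its unadjusted value gives the factor 1 − r²; adjusted power is 76%, 84% and 95%. With all 44 and 22 patients contributing, the figures are 76% unadjusted and 80%, 87% and 96% adjusted.

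**Simulation check** (4,000 trials per setting, 40 versus 20, normal data, 0.70 SD at every post-baseline visit). The week-4 t-test had power 70% to 71%; week-4 analysis of covariance had 74%, 82% and 94%. With no true effect, every method rejected in about 5% of trials.

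**Repeated measures analysis of variance, by reading:**

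- *Week 0 included, group main effect read as treatment effect.* The estimate is the average over five visits, one of which has no effect: 4/5 × 0.70 = 0.56 SD (simulated mean 0.56). Simulated power is 86%, 73% and 63%, against 98%, 98% and over 99% for analysis of covariance on the post-baseline mean.
- *Week 0 included, group-by-time read as the treatment test.* There is no dilution. Simulated power is 57%, 72% and 93%, against 74%, 82% and 94% for week-4 analysis of covariance.
- *Week 0 excluded, group main effect.* There is no dilution, but baseline is unused. Simulated power is 96%, 88% and 81%, against the same 98%, 98% and over 99%.

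**The case against.** The strongest reply is that a short statistical paragraph in a journal article leaves covariates, covariance structure and visit contrasts to the analysis plan. That holds for the unstated details. It does not remove the point, because the article commits to two-sample tests, which take no covariate, and no other section supplies the adjustment.

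Other replies stand and limit the point:

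- Unadjusted tests are valid under randomisation. The secondary outcomes have no stated power target, and the primary EASI50 is already defined relative to baseline.
- Randomisation is stratified by severity and lesions must cover less than 10% of body surface, which limits baseline EASI imbalance. It does not balance scores within a severity class, nor VAS or DLQI.
- The gain depends on r. At r = 0.3 it is small; at r = 0.7 the group-by-time test comes close to the adjusted week-4 comparison (93% against 94%).

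Three stronger readings are tempting, and the document does not support them. A reader might infer that baseline *is* averaged into the treatment effect; that requires both week 0 as a level of time and the group main effect as the treatment test, and the text fixes neither. A reader might infer that equal correlation between visits is assumed; that applies to the uncorrected univariate form, and the form is not stated. A reader might infer that no week-4 or week-16 difference will be available; the named t-test or Wilcoxon test can be applied at each visit.

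**Conclusion.** The point holds as a loss of efficiency on EASI, VAS and DLQI as secondary outcomes. Relative to baseline adjustment, the unadjusted visit comparison has variance 10%, 33% or 96% larger at r = 0.3, 0.5 or 0.7. The direction holds for any nonzero correlation, apart from a negligible loss of degrees of freedom; the size rests on the assumed correlations, equal SDs and, for power, the assumed 0.70 SD.

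The shrinkage by one fifth is conditional on a reading that the text leaves open and on an effect that is constant after baseline. Nothing here inflates type I error or touches the primary analysis or the sample size. It should be changed because the better method is free, not because the stated one is invalid.

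**What to change.** For the continuous secondary outcomes only, specify a baseline-adjusted analysis of the post-baseline visits (weeks 1, 2, 4 and 16). Either form will do:

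- a mixed model for repeated measures with baseline score, visit, treatment, treatment-by-visit and the stratification factors; or
- analysis of covariance at each visit with baseline score, treatment and the stratification factors.

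Severity overlaps baseline EASI and may be left out of the EASI model. Report the adjusted difference with its 95% confidence interval at week 4 and week 16. State how the chosen model works with the multiple imputation already planned. If repeated measures analysis of variance is kept as a supporting analysis, say whether week 0 is a level of time and which term tests treatment.

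Keep the t-test/Wilcoxon rule for other quantitative variables, such as age and body mass index.

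The cost is wording in the analysis plan. No new data, visits or patients are needed, the models run in the stated SAS 9.4, and analysis is not due to start until August 2026.

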### Outcomes

#### Primary outcome

The primary outcome indicator in this study is the EASI_50_ achievement rate at week 4. The EASI_50_ achievement rate is defined as proportion of patients achieving ≥50% improvement in EASI score from baseline to week 4.

The EASI score encompasses two main components: the affected body surface area (BSA) score (A) and clinical features score (B) for areas including the head and neck, trunk, upper limbs, and lower limbs (22). Component (A) evaluates the percentage of affected BSA for each area, which is scored on a scale of 0 to 6, as follows: 0 (0%), 1 (<10%), 2 (10–19%), 3 (20–49%), 4 (50–69%), 5 (70–89%), and 6 (90–100%). Component (B) assesses four critical clinical features: erythema (E), edema/papules/infiltration (I), excoriation (Ex), and lichenification (L). Each feature is scored based on severity, ranging from 0 to 3 points (0 = none, 1 = mild, 2 = moderate, 3 = severe). The overall EASI score is calculated by multiplying the product of (A) and (B) by regional weighted coefficients (ranging from 0.1 to 0.4) and summing these values across all regions. The total EASI score ranges from 0 to 72 points, with higher scores indicating greater severity. Based on the EASI score, the skin lesion condition of AD patients is categorized as mild (0–7 points), moderate (8–21 points), or severe (>21 points). In this study, the EASI score will be assessed at baseline (week 0), and at weeks 1, 2, 4, and 16.

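### The repeated measures ANOVA planned for EASI, VAS and DLQI names no sphericity correction; with visits 1, 1, 2 and 12 weeks apart, its standard group-by-time test may run at about 6.5-9.5% instead of 5%

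*Protocol article*

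**What the plan says.** The Secondary outcomes section of the protocol article lists the measures: "The secondary outcome indicators include the EASI, Visual Analogue Scale (VAS), Investigator’s Global Assessment (IGA), and Dermatology Life Quality Index (DLQI"). It fixes the visits: "These indicators will be assessed at baseline (week 0) and subsequently at weeks 1, 2, 4, and 16".

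The Statistical analysis section gives the method for such data in one sentence: "Repeated measurement data will be analyzed using repeated measures analysis of variance". It names no covariance structure, epsilon correction, contrast or error term. For single comparisons between arms it names another method: "For inter-group comparisons of quantitative variables with normal distribution, the Student *t*-test will be utilized", with the Wilcoxon rank-sum test for skewed data. The threshold is common to all tests: a p-"value of less than 0.05 (two-tailed) is viewed as statistically significant".

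The primary outcome is of a different kind: "The primary outcome indicator in this study is the EASI_50_ achievement rate at week 4". It is a proportion at one visit, and the section assigns categorical variables to chi-square or Fisher's exact tests.

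**The concern.** In its standard univariate form, repeated measures ANOVA tests group by time against one pooled within-patient error. The F distribution used for the p-value is right only under sphericity, that is, when the difference between any two visits has the same variance. Here two visits can be one week apart (weeks 1 and 2) or sixteen weeks apart (baseline and week 16). Scores from neighbouring weeks will usually be more alike than scores four months apart.

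Other design features point the same way. Under Interventions, the corticosteroid cream runs for 2 weeks and the urea ointment for 4, so week 16 falls 12 weeks after the last background treatment ends. EASI is bounded at zero and the trial expects most treated patients to halve it by week 4, so the spread may also change over time.

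When sphericity fails, the uncorrected test rejects too often. At stake is the error rate of the group-by-time test behind the secondary claims on lesions, itch and quality of life.

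**Working it through.** **Inputs from the article.** Visits at weeks 0, 1, 2, 4 and 16; 44 and 22 patients; two-sided 0.05; repeated measures ANOVA. The article gives no type I error for this test beyond the nominal 5%. Its only computed figure is the sample size, which supplies the arm sizes. With p1 = 0.85, p2 = 0.50 and k = 2, the article's formula gives

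n2 = [(0.85 × 0.15)/2 + 0.50 × 0.50] / 0.35² × (1.960 + 0.842)² = 20.1, and n1 = 2 × 20.1 = 40.2.

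This agrees with the stated 20 and 40. Adding 10% gives 22 and 44.

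**Inputs assumed.** The article gives no between-visit correlation or SD. The main assumption is a correlation of ρ^(weeks apart) with ρ from 0.7 to 0.95 per week and equal SDs. Compound symmetry (correlation 0.5 between all visits) is the reference case.

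**Step 1: how far from sphericity?** With equal SD σ, Var(Yj − Yk) = 2σ²(1 − ρ^|tj − tk|). Compare baseline to week 16 with week 1 to week 2:

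- ρ = 0.7: (1 − 0.7^16)/(1 − 0.7) = 0.997/0.30 = 3.3
- ρ = 0.9: (1 − 0.9^16)/(1 − 0.9) = 0.815/0.10 = 8.1
- ρ = 0.95: (1 − 0.95^16)/(1 − 0.95) = 0.560/0.05 = 11.2

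Sphericity would make each ratio 1.

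**Step 2: the test.** With five visits and 66 patients, the uncorrected F test has 5 − 1 = 4 and 4 × (66 − 2) = 256 degrees of freedom. Greenhouse-Geisser multiplies both by the estimated epsilon, which is 1 under sphericity.

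**Step 3: rejection rate under the null.** Simulated normal, complete data with the same covariance in both arms; 20,000 data sets per row at 44/22 and 10,000 at 40/20. The last two columns are at 44/22.

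| Correlation | Epsilon | Uncorrected F, 44/22 | Uncorrected F, 40/20 | Greenhouse-Geisser | Multivariate test |
|---|---|---|---|---|---|
| Compound symmetry | 1.00 | 5.0% | 5.3% | 4.6% | 5.1% |
| 0.7 per week | 0.74 | 6.6% | 6.9% | 4.6% | 4.7% |
| 0.8 per week | 0.63 | 7.6% | 7.0% | 4.8% | 5.1% |
| 0.9 per week | 0.51 | 8.5% | 8.7% | 4.8% | 4.8% |
| 0.95 per week | 0.45 | 9.3% | 9.5% | 5.0% | 5.1% |

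The simulation standard error at 20,000 runs is √(0.05 × 0.95/20,000) = 0.15 percentage points near 5% and √(0.09 × 0.91/20,000) = 0.20 near 9%.

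**Step 4: sensitivity.**

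- If correlation falls per visit rather than per week (0.5 to 0.9 between neighbouring visits), the uncorrected test runs at 5.9-8.2%.
- Over all 18 structures tried, including rising and falling SDs, it runs at about 5-10%, Greenhouse-Geisser at 4.2-5.2% and the multivariate test at 4.7-5.4%.
- With baseline as a covariate and the four later visits as outcomes, the uncorrected test runs at 6.3-8.4% for decay of 0.7 to 0.95 per week. Baseline adjustment alone therefore reduces the problem without removing it.

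**The case against.** **The sentence does not say that the test will be uncorrected.** Greenhouse-Geisser, Huynh-Feldt and multivariate versions also go by the name of repeated measures ANOVA, and the simulated rates for these stay near 5%. A journal article commonly leaves the choice to a full protocol or analysis plan, which is not shown. This stands: the standard form is an inference, and the text is unspecific rather than plainly wrong. The point survives because the article does name a method, and the method's standard form suits this visit schedule poorly. The version also matters. With decay of 0.8 to 0.95 per week, the uncorrected test was significant and Greenhouse-Geisser was not in 2.5-4.3% of null data sets.

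**The inflation rests on correlations that nobody has given.** This also stands. A reader might infer that sphericity is certain to fail and that the test runs at 8-9%. The article does not support that as a fact. Those rates need strong serial correlation, and under compound symmetry there is no inflation.

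**A reader might go further and infer that comparisons at single visits are badly off.** A week-16-minus-baseline contrast that borrowed the ANOVA's pooled error would reject in up to about 20% of null trials under strong serial correlation, and early-visit contrasts could be too strict. But the article plans no such contrast. It sends quantitative comparisons between arms to a t-test or a Wilcoxon test, and a t-test on the week-16 change held 4.3-5.3% in the same simulations. That reading falls.

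**A mixed model is not the only valid remedy.** Agreed; a named correction also controls the error rate.

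**Conclusion.** The concern holds in a limited, conditional form. If the standard uncorrected group-by-time F test is used, and if within-patient correlation decays by 0.7 to 0.95 per week, its type I error is about 6.5-9.5% against a nominal 5%, or about 6-8.5% with baseline as a covariate. Under compound symmetry it is 5%. The figures assume normal, complete data and equal covariance in the two arms.

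The reach is the group-by-time test for EASI, VAS and DLQI as secondary outcomes. The week-4 responder analysis and the sample size built on it are unaffected. No claim is made about the error rate of comparisons at single visits. This is a modest weakness in a stated method that is cheap to remove before the data are analysed.

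**What to change.** Replace the sentence on repeated measurement data with text such as: EASI, VAS and DLQI at weeks 1, 2, 4 and 16 will be analysed with a mixed model for repeated measures with unstructured covariance and Kenward-Roger degrees of freedom, and the difference between arms with its 95% CI will be reported at each visit.

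If ANOVA is kept, add that the group-by-time test will be based on the Greenhouse-Geisser p-value. In the simulations this correction held about 5%, as did the multivariate test, which also leaves the covariance unstructured. The mixed model with Kenward-Roger degrees of freedom was not itself part of the re-run simulations.

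The change uses data already scheduled and is standard code in the named software ("data analysis will be conducted using the SAS 9.4 statistical software"). It does not conflict with the missing-data plan ("Missing data will be addressed under the missing-at-random assumption using sequential regression multiple imputation"), since a likelihood-based mixed model rests on the same missing-at-random assumption. The cost is one sentence and slightly fewer error degrees of freedom.

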### Randomization

In this study, stratified randomization will be employed, with stratification factors including patient gender (male, female) and disease severity (mild, moderate). A total of 66 patients with mild-to-moderate atopic dermatitis (AD) will be randomly assigned to either the treatment group or the control group in a 2:1 ratio, based on these stratification factors. Randomization will be performed by an independent statistician using the clinical research support system to generate 66 random numbers. Allocation concealment will be ensured through the use of sequentially numbered, opaque envelopes, which will be securely stored with restricted access at the clinical research center of Shanghai Skin Disease Hospital.

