### Interventions

Patients in the treatment group will take a daily bath using MSS for a period of 4 months. To ensure the proper application of MSS, dermatologists will advise patients to first moisten their entire body with warm water, then apply 8 g of the product (4 g per press) to the skin surface. Massage gently for 3 to 5 min to ensure full absorption, and followed by rinsing with warm water. Patients in the control group will also take a daily bath using MSS placebo for a period of 4 months. The MSS placebo was formulated to be devoid of any Chinese herbal constituents, containing only the base excipients. It was manufactured by the same entity to guarantee perfect consistency with the active treatment in all physical attributes—appearance, weight, color, odor, and packaging. The guidance and application of MSS placebo in the control group will be identical to that for the treatment group.

In this study, both of patients in the treatment group and control group will receive the same foundational therapeutic regimen. The foundational therapies include desonide cream for mild AD and triamcinolone acetonide cream for moderate AD, both of which will be applied twice daily for 2 weeks. Additionally, all patients will receive urea ointment twice daily for 4 weeks. In this study, no additional treatment is permitted, and emergency interventions require documentation in detail and will result in the withdrawal of participation.

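### The only stated test for a binary outcome ignores the randomisation strata and leaves chi-square or Fisher open; one stratified primary test should be named in advance

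*Protocol article*

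**What the plan says.** All references are to the Protocol article.

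- **Primary outcome:** the endpoint is binary: "The primary outcome indicator in this study is the EASI_50_ achievement rate at week 4".
- **Randomization:** allocation is 2:1 with "stratification factors including patient gender (male, female) and disease severity (mild, moderate"), which gives four strata.
- **Interventions:** severity also decides the background steroid: "desonide cream for mild AD and triamcinolone acetonide cream for moderate AD".
- **Statistical analysis:** categorical variables are given as frequencies and proportions, "with differences between groups evaluated through chi-square tests" or Fisher's exact tests. No stratum, covariate or rule for choosing between the two tests is given, and no separate primary analysis is named. The same section prescribes analysis of all randomised patients, multiple imputation of missing data, and a p-value "of less than 0.05 (two-tailed) is viewed as statistically significant".
- **Sample size:** response "would be 85% in the treatment group and 50% in the control group", a two-tailed "level at 0.05 and statistical power at 80"%, 40 and 20 patients required, 44 and 22 enrolled. The formula shown is for two unstratified proportions.

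**The concern.** Stratified randomisation balances the arms on severity. If severity predicts response, the true variance of the difference between arms is then smaller than an unstratified test assumes, so the test rejects less often than its nominal level allows. A prognostic effect of severity is plausible, because the sponsor chose it as a stratification factor and gives its two levels different steroids.

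The second matter is the open choice between two tests. At this sample size they differ by several points of power, and they can fall on opposite sides of 0.05 in the same data. With no selection rule in the text, the result of a borderline trial could depend on which one is run.

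**Working it through.** **Inputs.** From Sample size: 85% and 50% response, two-sided alpha 0.05, 80% power, ratio k = 2, 40/20 evaluable and 44/22 enrolled. From Randomization: four strata. Response by severity is not in the document, so it is assumed and varied below.

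**1. The plan's own figure.** The protocol formula gives

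n2 = [0.85 × 0.15 / 2 + 0.50 × 0.50] / 0.35² × (1.960 + 0.842)² = 0.31375 / 0.1225 × 7.85 = 20.1, and n1 = 2 × 20.1 = 40.2.

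The stated 40 and 20 are reproduced. Then 40 × 1.1 = 44 and 20 × 1.1 = 22.

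**2. Power of the two named tests,** by exact enumeration of the two binomials at 85% and 50%, without strata. The fallback row uses the customary rule of switching to Fisher if an expected count is below 5. The protocol does not state that rule.

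| Test | 40/20 | 44/22 |
|---|---|---|
| Chi-square | 82.3% | 86.4% |
| Fisher | 77.2% | 82.0% |
| Chi-square with Fisher fallback | 79.0% | 84.4% |
| Share of trials sent to Fisher | 32% | 18% |
| Chi-square and Fisher disagree at 0.05 | 5.1% | 4.4% |

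The fallback is used often because the smallest expected cell is close to 5. At 40/20 it is 20 × (6 + 10) / 60 = 5.3, and at 44/22 it is 22 × (6.6 + 11) / 66 = 5.9.

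**3. Level of the unstratified test when severity is prognostic.** Assume equal severity strata and null response rates of 80% and 40% in both arms, so 60% overall.

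- Variance used by the unstratified test: 0.6 × 0.4 = 0.24.
- Average variance within strata: (0.8 × 0.2 + 0.4 × 0.6) / 2 = 0.20.
- With balanced strata the z statistic has SD √(0.20/0.24) = 0.913, so the real level is 2 × [1 − Φ(1.96/0.913)] = 2 × [1 − Φ(2.147)] ≈ 3.2%.

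Simulation gives 3.1 to 3.3% for chi-square and 4.9% for CMH.

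**4. Power and level over a range of severity effects.** This is a simulation with 100,000 replicates and four near-equal strata in which only severity is prognostic. Overall rates are held at 85% and 50% for power, and at 70% in both arms for type I error.

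| Severity odds ratio | Power 40/20: chi-square / CMH / Fisher | Power 44/22: chi-square / CMH / Fisher | Type I error 44/22: chi-square / CMH |
|---|---|---|---|
| 1 | 82.4 / 82.7 / 77.2% | 86.3 / 85.5 / 81.9% | 5.1 / 4.9% |
| 3 | 83.0 / 84.3 / 77.8% | 87.2 / 87.4 / 82.8% | 4.5 / 4.9% |
| 5 | 83.7 / 85.9 / 78.3% | 88.0 / 89.1 / 83.6% | 3.9 / 5.0% |
| 8 | 84.7 / 87.9 / 79.4% | 88.9 / 90.8 / 84.7% | 3.2 / 4.9% |

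CMH minus chi-square runs from about -1 point (44/22, no severity effect) to about +3 points (40/20, odds ratio 8). CMH minus Fisher is about 4 to 6 points at 44/22 and 5 to 9 points at 40/20.

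**The case against.** Several stronger readings are tempting, and the document does not support them.

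- **That ignoring the strata wastes much power.** Most of the apparent gain from CMH is a gain over Fisher. With assumed response by severity of 95/75% on treatment and 65/35% on control, at 40/20, power is 80.2% with the fallback rule, 83.8% with chi-square and 85.5% with CMH. Of the 5.3 points between the first and last, 3.6 come from Fisher and 1.7 from the strata.
- **That the trial falls short of its planned 80% power.** This is so only for Fisher or the fallback at 40/20. The plan analyses all randomised patients with imputation. At 44/22 every option exceeds 80% on complete data, although imputation would lower all of them somewhat.
- **That the open choice threatens the type I error.** In these tables, taking the smaller of the two p-values always equals taking chi-square. Without strata its level is 4.4 to 5.5% for common response rates from 50% to 85%. The problem is discretion over a borderline result, with hardly any inflation of alpha.
- **That response certainly differs by severity.** No rates by severity are given. EASI50 is relative to each patient's own baseline and the steroid is matched to severity, and either could narrow a difference.
- **That multiple imputation calls for stratification.** A Fisher p-value cannot be pooled by Rubin's rules, but neither can a raw CMH statistic. An unstratified risk difference with its standard error can be pooled too.

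It is also fair to say that the sentence on categorical variables is general and does not name EASI50, that the unstratified test agrees with the unstratified sample size formula, and that an analysis plan not shown may add a selection rule or an adjusted analysis. These points lower the weight of the concern. What stands is that the published method, the only one given for a binary outcome, does not follow the stated randomisation.

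**Conclusion.** The point holds as a modest mismatch between design and analysis. The unstratified test is valid but conservative if severity is prognostic: about 3% instead of 5% under assumed null rates of 80% and 40%, and less so for weaker effects (4.5% at an odds ratio of 3). The power cost against chi-square is about -1 to +3 points. The larger cost, 4 to 5 points without any stratum effect, comes if Fisher is used, and the text leaves that open.

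The figures for strata rest on assumed response rates and near-equal strata. The comparison of chi-square with Fisher rests only on the protocol's own rates and sample sizes.

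**What to change.** Before data analysis starts, name one primary analysis: a CMH test of week-4 EASI50 stratified by the randomisation factors (severity, and gender unless the strata prove too sparse, with that condition set in advance). Report the Mantel-Haenszel risk difference with its 95% CI, estimated in each imputed data set and pooled by Rubin's rules. Keep the unstratified test as a sensitivity analysis and say which one it is.

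The cost is a sentence or two, with no new data, because both factors are known at randomisation. The sample size need not change. There is a small downside: about 1 point of power at 44/22 if the strata are not prognostic (85.5% against 86.3%), and sparse strata. Balanced strata would hold 22 / 4 = 5 to 6 controls each. If 80% of patients were mild (an assumption), each moderate stratum would hold about 22 × 0.2 / 2 = 2 controls and CMH would show no gain (86.4% against 86.7% for chi-square).
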